## Abstract

**Background:**

Ulcerative colitis (UC) is an intestinal inflammatory disease characterized by inflammation of the colonic mucosa. With unknown pathogenesis, it has become a chronic lifetime disorder worldwide. In patients with moderately active UC, several therapies (e.g., aminosalicylates, corticosteroids, immunosuppressants, and biologics) are recommended for induction (or maintenance) of remission. Given the side effects and disease burden, it is difficult for most patients to achieve ideal treatment goals in clinical practice. Chinese herbal medicine (CHM), as a complementary therapy, has been widely used in the management of UC in China. Qing-Chang-Hua-Shi granule (QCHS) is a classical Chinese herbal formula. Our preliminary study suggested that the QCHS decoction has a significant effect on patients with moderately active UC. However, its effectiveness and safety has not been evaluated convincingly. Therefore, we designed this protocol to investigate the efficacy of QCHS granule for moderately active UC.

**Methods:**

This is a multicenter, randomized, double-blind, placebo-controlled, superiority trial. A total of 120 patients with moderately active UC will be recruited from 10 hospitals in China. Each eligible participant will be randomly assigned to receive QCHS granule or placebo for 12 weeks. Both groups will be given basic treatment with mesalazine (4 g/day). The primary outcomes are the clinical response (remission) rate. The secondary outcomes are health-related quality of life, endoscopic response rate, mucosal healing rate, and inflammatory markers (e.g., fecal calprotectin and CRP). The whole study period will last 36 weeks, including 24 weeks follow-up time. According to the intention-to-treat principle, variables will be assessed at 2, 4, 6, 8, 10, and 12 weeks after study commencement.

**Discussion:**

This is the first randomized controlled clinical study protocol regarding Chinese herbal extract granules in the management of moderately active UC. We aim to investigate the superiority of QCHS granules over placebo in terms of induction of remission. If the trial shows significant benefits of QCHS granules, it will help clinical practitioners, UC patients, and policymakers make more informed choices in the decision-making.

**Trial registration:**

Chinese Clinical Trial Registry ChiCTR-IOR-14005554. Registered on 27 November 2014.

**Supplementary Information:**

The online version contains supplementary material available at 10.1186/s13063-020-05012-8.

## Background

Ulcerative colitis (UC) refers to a subtype of inflammatory bowel disease (IBD), which is characterized by chronic idiopathic inflammation of the large intestine (e.g., colonic mucosa) [1, 2]. As a lifelong disease [3, 4], UC has a significant impact on health-related quality of life [5, 6]. To date, the pathogenesis mechanism of UC is not fully understood, associated with multiple factors (e.g., heredity, environment, immunity, and behavior) [7, 8]. As a result, it has become a global refractory disease with worldwide shifting epidemiological characteristics. According to a recent survey, the incidence and prevalence in developed areas such as North America and Europe have been stable [9]. However, the data in Asia and other developing countries have encountered a significant increase over the past decade [10, 11]. Currently, the optimal goal of management is to induce (steroid-free) remission, maintain remission, and prevent disease-related complication and health-related quality of life [12]. Besides, it is believed that an emerging goal in UC management is mucosal healing. To achieve these goals, 5-aminosalicylic acid, corticosteroids, immunosuppressants, biological agents, and other promising treatments (e.g., fecal microbiota transplantation) have been developed one by one [13]. As a consequence, budesonide, corticosteroids, and anti-TNF therapy (e.g., adalimumab, golimumab, and infliximab) have been strongly recommended to induce remission for moderately active UC with moderate to high quality of evidence [14]. However, many patients do not react well to these conventional drugs in clinical practice. What is worse, most of these treatments have limitations in safety and efficacy, such as serious side-effects, long course of treatment, heavy burden of disease, and so on [15, 16]. Therefore, there still seems to be room for improvement in the management of moderately active UC.

Historically, in Asia (especially in China), Chinese herbal medicine (CHM) has been widely used for UC due to the unique advantages of efficacy and safety [17]. Under the circumstance, an increasing amount of evidences have shown that CHM have potentially positive effects on UC [18–20]. According to the theory of traditional Chinese medicine (TCM), CHM plays an irreplaceable role in the management of UC.

Over the past decade, our group has been searching for Chinese herbs that can be used for UC. Through years of our clinical practice, we found that QCHS formula developed from classical Chinese herbal formulas could not only relieve patients’ clinical symptoms, but also promote mucosal healing by adjusting the balance of the body. Our previous studies in vivo have proved that QCHS was associated with significant benefits regarding ameliorating the damage to colon length, suppressing inflammatory cytokines and mediators, alleviating oxidative stress through β2AR/β-arrestin2/NF-κB signaling pathway [21, 22]. Furthermore, QCHS could significantly inhibit apoptosis in HT-29 cells through MEK/ERK signaling via SGK1 [23]. However, our preliminary studies were limited to systematic top-level design (e.g., small sample size, placebo effect). Given these findings, the evidence of its effectiveness and safety was unconvincing, especially in patients with moderately active UC. Under the circumstance, we designed this protocol, a prospective, multicenter, randomized, double-blind, placebo-controlled, superiority trial, to further determine the efficacy and safety of QCHS granule combination therapy for UC patients who do not respond to 5-ASA after 4 weeks. We predict that patients with moderately active UC will benefit in terms of clinical remission, mucosal healing, and quality of life.

## Hypothesis and objective

In our protocol, we hypothesize that QCHS granule combined with basic treatment (5-ASA) is superior to placebo plus 5-ASA on clinical response (remission) rate, mucosal healing rate, clinical syndromes, quality of life, inflammatory mediators (e.g., fecal calprotectin, TNF-α, and hs-CRP), and adverse side-effects.

The primary objective of this trial is to investigate the efficacy of QCHS granule combined with 5-ASA in the management of patients with moderately active UC. Furthermore, the secondary objective is to explore the safety of QCHS granule for moderately active UC.

## Methods

### Study design

This is a prospective, multicenter, randomized, double-blind, placebo-controlled, superiority clinical trial, which conforms to the Consolidated Standards of Reporting Trials (CONSORT) 2010 statement guidelines [24], the Standard Protocol Items: Recommendations for Interventional Trials (SPIRIT) 2013 Statement [25], and the Standard Protocol Items for Clinical Trials with Traditional Chinese Medicine: Recommendations, Explanation and Elaboration (SPIRIT-TCM) Extension 2018 Statement [26]. The study began in January 2016 and will last until October 2022. A total of 120 eligible patients will be enrolled and randomized into the QCHS granule group or the placebo group. All patients will voluntarily sign the informed consent prior to enrollment. Prior to allocation, each of them will be screened by the eligibility criteria. According to patients’ included sequence number equally, block randomization will be performed to ensure equal group sizes with an allocation of 1:1 (permuted block sizes of 6). Participants in the QCHS granule group will receive QCHS granule (125 g daily, orally) for continuous 12 weeks, while patients in the placebo group will receive QCHS granule placebo (125 g daily, orally) for the same duration. Both groups will be given basic treatment with mesalazine (5-aminosalicylic acid, 4 g/day). Researchers and patients will be blinded from the beginning of the trial. All interested outcomes including patient-reported outcomes will be collected before (0 weeks) and after intervention (2 weeks, 4 weeks, 6 weeks, 8 weeks, 10 weeks, and 12 weeks). The whole study period will last 36 weeks, including 24 weeks of follow-up. The complete SPIRIT (2013) checklist and SPIRIT-TCM (2018) checklist for the study are provided in Additional files 1 and 2. The overview and the SPIRIT schedule of the study are illustrated in Figs. 1 and 2, respectively.

**Fig. 1 Fig1:**
[figure not shown]
Overview (flowchart) of the protocol

**Fig. 2 Fig2:**
[figure not shown]
Schedule of enrolment, interventions, assessments, and follow-up

### Ethics and registration

The protocol has been approved by the Ethics Committee of Affiliated Hospital of Nanjing University of Chinese Medicine (approval number:2014NL-074-02, Additional file 3). Each subcenter applied for local institutional review boards (IRBs) approval. Furthermore, this trial has been registered on the Chinese Clinical Trial Registry (URL: http://www.chictr.org.cn/, No. ChiCTR-IOR-14005554).

### Sample size and power calculation

The sample size was calculated according to the primary outcome (clinical response rate) at 12 weeks after initiation. The sample size calculation was based on the comparison of the proportions in the QCHS granule group versus the placebo group. On the basis of previous study and clinical experience, we predicted that the clinical remission rates at 12 weeks would be 79% in the QCHS granule group and 41% in the placebo group [27, 28]. A difference of 10% was selected as the smallest difference that would be of clinical significance. For a two-sided significance level of 0.05 (*α* = 0.05), it is estimated that a sample size of 54 subjects per group will be required to detect the superiority of QCHS granule over placebo with a test power of 80%. Under the hypothesis that some patients are unable to follow-up or unsuitable for analysis, the sample size will be inflated. Considering 10% drop out, the total planned sample size will be 60 per group.

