### Statistical analysis

According to our protocol, all data analyses will be conducted based on pre-established statistical analysis plan. All analyses of data will be performed by SAS software (v. 9.3; SAS Institute Inc., Cary, NC, USA). To ensure the consistency and reliability of the conclusions, both intention-to-treat (ITT) analysis and per-protocol (PP) analysis will be done if necessary. All missing data will be imputed by multiple imputation. Statistical description will be performed with frequency, mean, median, standard deviation, lower quartile (P25), upper quartile (P75), minimum, and maximum. Normality of all quantitative (continuous) variables (e.g., demographic characteristics, vital signs, biochemical parameters) will be tested by the Kolmogorov-Smirnov test. For normal distribution data, independent sample *t* test and paired sample *t* test will be employed to compare parameters at the beginning and the end of the study between and within groups, respectively. For abnormal distributions data (e.g., quality of life, inflammation markers), the Mann-Whitney *U* test and Wilcoxon signed-rank test will be used instead. For qualitative (categorical) variables, the chi-square test or Fisher’s exact test will be used, such as clinical response rate, endoscopic response rate, and mucosal healing rate. In the evaluation of efficacy and analysis of influencing factors, center and disease will be used as covariates. Covariance analysis (ANCOVA) will be used [35]. Multiple linear regression or logistic regression will be used to analyze the influencing factors and evaluate the effect of gender and condition on the efficacy of the two groups. For all analyses, *P* < 0.05 will be considered statistically significant.

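### The stated 54 per group at 80% power does not follow from 79% vs 41% and the planned chi-square or Fisher test, which need about 25 to 30 per group; the role of the 10% difference is not stated

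*Protocol article*

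**What the plan says.** All the planning figures are in the protocol article, Sample size and power calculation:

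- Basis: "The sample size calculation was based on the comparison of the proportions in the QCHS granule group versus the placebo group".
- Expected rates at 12 weeks: "79% in the QCHS granule group and 41% in the placebo group". The section says the size rests on clinical response, yet labels these two figures as remission rates.
- Clinical relevance: "A difference of 10% was selected as the smallest difference that would be of clinical significance". Nothing says whether or how this entered the formula.
- Error rates: "For a two-sided significance level of 0.05", and "with a test power of 80"%.
- Result: "it is estimated that a sample size of 54 subjects per group will be required to detect the superiority of QCHS granule over placebo".
- Inflation: "Considering 10% drop out, the total planned sample size will be 60 per group".

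Allocation is 1:1 (Randomization, allocation concealment, and blinding). The Outcomes section makes clinical response the primary outcome. Under Statistical analysis, categorical outcomes, "such as clinical response rate, endoscopic response rate, and mucosal healing rate", are compared by the chi-square test or Fisher's exact test, with P < 0.05 as the threshold. Both tests have a null hypothesis of no difference. That section also mentions covariance analysis and regression for covariates, but no comparison with a 10-point threshold.

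**The concern.** A difference of 38 percentage points between 79% and 41% is very large, and 54 per group is about twice what a comparison of two proportions needs at 80% power. So either the stated power, the stated sample size or the description of the method is wrong. The 10% sentence is the only other number in the section that could have raised the result, and its role is left open.

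Two things are at stake. First, the power statement will be carried into the trial report, and it is not the power of the planned test. Second, the reader cannot tell whether success means a difference from zero or a difference larger than 10 points, and the two criteria can give different answers on the same data.

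**Working it through.** **Inputs.** p1 = 0.79, p2 = 0.41, difference 0.38, two-sided alpha 0.05 (z = 1.960), power 80% (z = 0.842), 1:1 allocation. Mean rate 0.60. Variance terms:
- V1 = 0.79 × 0.21 + 0.41 × 0.59 = 0.4078 (unpooled)
- V0 = 2 × 0.60 × 0.40 = 0.48 (pooled)

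**Step 1: the plan's figure with a null of no difference.**
- Unpooled: V1 × (1.960 + 0.842)² / 0.38² = 0.4078 × 7.849 / 0.1444 = 22.2
- Pooled under the null, the usual chi-square formula: (1.960 × √0.48 + 0.842 × √0.4078)² / 0.1444 = 24.9, i.e. 25
- Pooled throughout: 0.48 × 7.849 / 0.1444 = 26.1
- Continuity correction, n/4 × (1 + √(1 + 4/(n × 0.38)))²: 27.2, 29.9 and 31.1 for the three versions
- Fisher's exact test, exact power: 73.9% at 25 per group, 80.6% at 30

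The range is about 22 to 31 per group. The figure of 54 is not reproduced.

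**Step 2: power at 54 per group for the planned tests** (exact binomial, 79% vs 41%). Chi-square 98.7%, Fisher 97.9%. The normal approximation for chi-square gives 98.8%.

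**Step 3: could 10% have been a superiority margin?** Put a 10-point margin in the null, so that the distance becomes 0.38 − 0.10 = 0.28 and its square 0.0784.

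| Variance | 80% power | 80% power, continuity-corrected |
|---|---|---|
| Unpooled | 40.8 | 47.7 |
| Pooled under the null | 45.8 | 52.7 |
| Pooled throughout | 48.1 | 55.0 |

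Unpooled at 90% power gives 54.7. The margin alone therefore stops at about 48. Coming near 54 takes a second ingredient that the article does not state, and no version gives exactly 54. A zero-difference calculation at 99% power also lands nearby (52 unpooled, 56 pooled).

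**Step 4: could 10 points have been the target effect?** Detecting 51% vs 41% needs 389 per group, and 79% vs 69% needs 301. This is not the source of 54 either. Exact power for 51% vs 41% with 54 per group is 17% (chi-square) or 12% (Fisher).

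**Step 5: what 54 per group detects against 41%.** Chi-square reaches 80.1% power at 68% (27 points), where Fisher has 74.4%. Fisher has 78.0% at 69% and 81.3% at 70%, so it needs about 29 points.

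**Step 6: what the two criteria would require of the data.** Illustration with 60 per group and 25/60 placebo responders:
- Chi-square significance: 36/60, an 18-point observed difference (z = 2.01)
- Fisher significance: 37/60, 20 points (P = 0.044; 36/60 gives P = 0.067)
- Wald 95% lower limit above 10 points: 42/60, 28 points (lower limit 11.3; 41/60 gives 9.5)

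**Step 7: dropout.** 54 / 0.9 = 60. This part is correct.

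**The case against.** The strongest reply is that the discrepancy does no harm. More patients than needed were planned, type I error is untouched, and the trial has ample power at the stated rates. This stands, and it limits the point to a wrong stated figure.

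A second reply is that the article condenses the full protocol and defers to a separate statistical analysis plan, where a margin rule may be written. This also stands as far as it goes: one can say that the article states no test against 10 points, not that none exists. It does not rescue the arithmetic, because the section gives its own inputs and they do not produce its own result.

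Two stronger readings are tempting. A reader might infer that the trial was sized on a 10-point margin, and hence that sample size and analysis answer different questions. The article does not support this: it never calls 10% a margin, and a margin reaches the neighbourhood of 54 only with an unstated continuity correction or unstated 90% power. A reader might also infer that the trial claims power to detect 10 points. It does not: it states the expected rates as 79% and 41%, and calls 10% only the smallest difference that would matter clinically.

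**Conclusion.** The stated combination of 54 per group and 80% power is wrong for the tests named in the article. The stated inputs need about 25 per group (30 with continuity correction or Fisher's test), and 54 per group gives about 98 to 99% power. How 54 was obtained cannot be determined from the document, and the role of the 10% is undefined.

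The error is conservative for the zero-difference test. It threatens neither type I error nor adequate size at the stated rates.

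The power figures assume independent binomial outcomes, 54 evaluable patients per group, no covariate adjustment, and that 79% and 41% apply to the primary outcome. The last assumption is not secure: the section calls them remission rates while the primary outcome is response. If they are remission rates, no power has been established for the primary outcome.

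**What to change.** Keep 60 per group and correct the text.

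1. Restate the power for the test to be run. For example: with 54 evaluable patients per group and two-sided alpha 0.05, power for 79% vs 41% is about 98% (98.7% chi-square, 97.9% Fisher). Against a placebo rate of 41%, 80% power is reached at a true difference of about 27 points with chi-square or about 29 points with Fisher. Power for a 10-point difference (51% vs 41%) is under 20%.
2. Say whether 79% and 41% are response or remission rates. If they are remission rates, give the response rates assumed and the power for them.
3. Settle the 10%. Either state that it is not part of the hypothesis or, if the trial was in fact sized on a 10-point margin, give the formula, variance and power used, and judge superiority by the 95% confidence interval of the risk difference against 10 points. Fix this before unblinding.

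The cost is wording in two sections and no extra patients. Only the margin option in item 3 has a further consequence, a stricter success criterion: in the illustration above, an observed difference of 28 points instead of 18 (chi-square) or 20 (Fisher).

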### Randomization, allocation concealment, and blinding

A total of 120 patients with moderately active UC will be randomized into the QCHS granule group or the placebo group with an allocation ratio of 1:1. Participants will be recruited from 10 hospitals in China by centralized computer-generated software. To ensure balance by study site, a stratified and block randomization algorithm was used and randomization was stratified by study site (12 cases in each center) and block sizes of six were used within each strata. The randomization allocation sequence generated by SAS 9.4 (SAS Institute Inc., Cary, NC, USA) was converted into unique serial numbers for each enrolled subject in subcenters. QCHS granule and placebo granule will be provided to each subcenter in advance, encoded and labeled with the above serial number. To ensure blinding, the QCHS granule and placebo granule will be identical in all aspects (e.g., appearance, size, color, smell, taste, containers, and doses). Participant and Principal Investigators will be blinded to group allocation throughout the research. The randomization procedure was conducted by an independent research assistant who is not involved in clinical observation or assessment. Under the supervision of Data Safety and Monitoring Board (DSMB), the randomization code will only be broken due to adverse events and statistical analysis.

### Participants

The participants will be 120 patients with moderately active UC diagnosed as per histologic and endoscopic criteria. The diagnostic criteria are based on the Second European evidence-based Consensus on the diagnosis and management of ulcerative colitis in 2012 [29] and Chinese Association of Integrative Medicine Guidelines for Diagnosis of UC in 2010 [30].

### Inclusion criteria

Patients will be included if they meet the following criteria:
Confirmed diagnosis of moderately active UC after taking 5-ASA for more than 4 weeks (total Mayo score between 6 and 10, endoscopy subscore > 2) [31]Confirmed diagnosis of TCM syndrome differentiation (large intestine damp-heat syndrome) [30]Males or females with age range between 18 and 50 yearsEthical principle who voluntarily sign the informed consent form

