### Outcomes

The primary outcome of this study is the clinical response rate in patients with moderately active UC. The clinical response refers to a decrease (from the baseline) of the total Mayo score by at least 30% (or 3 points) together with a decrease of the rectal bleeding subscore by at least 1 point (or rectal bleeding subscore of 0 or 1 point) with no individual subscore exceeding 1 point [32].

The secondary outcomes are as follows: health-related quality of life measured by the Inflammatory Bowel Disease Questionnaire (IBDQ) [33], endoscopic response rate defined as a decrease of Mayo disease activity index endoscopy subscore by at least 1 [32], mucosal healing rate defined as endoscopy subscore of Mayo disease activity index of 0 or 1, and improvements in inflammatory markers (e.g., fecal calprotectin, tumor necrosis factor-α and hypersensitive-C reactive protein, erythrocyte sedimentation rate) [34].

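### The endoscopic entry cut-off, read literally, admits only the top grade, which fits poorly with a population described throughout as moderately active

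*Protocol article*

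**What the plan says.** Under Inclusion criteria, the protocol article admits patients with moderately active UC after more than 4 weeks of 5-ASA and attaches the condition "total Mayo score between 6 and 10, endoscopy subscore > 2". This is the only place where an endoscopic entry threshold is given; no other section restates or corrects it.

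The label moderately active recurs in the Abstract, Hypothesis and objective, Randomization, Participants, Outcomes and Discussion. None of these sections limits the trial to the most severe endoscopic grade.

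Three definitions under Outcomes depend, or may depend, on the endoscopy subscore:
- "mucosal healing rate defined as endoscopy subscore of Mayo disease activity index of 0 or 1"
- "endoscopic response rate defined as a decrease of Mayo disease activity index endoscopy subscore by at least 1"
- the primary clinical response, whose closing condition is "with no individual subscore exceeding 1 point"

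**The concern.** A strict inequality at 2 on a scale that ends at 3 leaves one admissible value. The entry rule then selects patients at the worst endoscopic grade, while the title population and the planned conclusion concern moderately active disease. A patient with subscore 2 has unhealed mucosa by the article's own healing definition, yet would be ineligible whatever the total score.

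Two things are at stake. The first is applicability: a reader would take the conclusion to cover moderately active UC generally, when on the literal rule it covers only those at the top endoscopic grade. The second is the meaning of the endoscopic endpoints, because the entry grade fixes how far a patient must improve to count as healed. The comparison between arms is not at stake, since both arms pass through the same entry rule and randomisation is stratified by site.

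**Working it through.** No figure in the plan is derived from the endoscopic cut-off, so there is none to reproduce. The check is a reading of the rule against the scale and the endpoint definitions.

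**Inputs**
- Entry rule: total Mayo 6 to 10 and endoscopy subscore > 2 (Inclusion criteria).
- Mucosal healing: endoscopy subscore 0 or 1 (Outcomes).
- Endoscopic response: a fall of at least 1 in the endoscopy subscore (Outcomes).
- Assumption, not printed in the article: the Mayo score has four items, each graded in whole numbers from 0 to 3.

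**Step 1. Who satisfies the cut-off.** The values of {0, 1, 2, 3} above 2 are {3}. An inclusive sign would give {2, 3}. The step fails only if the subscore can exceed 3 or take values between 2 and 3, and nothing in the article suggests either.

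**Step 2. Whether the rule can be met with the total score.** With endoscopy at 3, the other three items must sum to between 6 − 3 = 3 and 10 − 3 = 7. Three items scored 0 to 3 have 4 × 4 × 4 = 64 combinations. Those with sums 3, 4, 5, 6 and 7 number 10 + 12 + 12 + 10 + 6 = 50. The rule is therefore not empty, and there is no arithmetic contradiction between the two halves of the criterion.

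**Step 3. Whether grade 2 is also compatible with the total score.** With endoscopy at 2, the other three items must sum to between 4 and 8, and 12 + 12 + 10 + 6 + 3 = 43 of the 64 combinations do so. The total-score range alone therefore does not rule out grade 2; the operator does.

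**Step 4. What the entry grade does to the endpoints.**

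| Entry grade | Fall needed for mucosal healing | Fall needed for endoscopic response | Relation of the two endpoints |
|---|---|---|---|
| 3 | 3 − 1 = at least 2 | at least 1 | 3 to 2 is response without healing |
| 2 | 2 − 1 = at least 1 | at least 1 | the same event |

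On the literal rule every patient is in the first row. On an inclusive rule the trial mixes both rows.

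**Step 5. The primary outcome.** If the condition "with no individual subscore exceeding 1 point" applies to the endoscopy item at week 12, a responder must also reach 0 or 1 and so fall by at least two grades from entry at 3. The wording does not settle whether it covers endoscopy, so this consequence is conditional.

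**The case against.** The strongest reply is that the criterion is itself the trial's definition of its population. Total activity and endoscopic grade are different quantities, and moderate overall activity with top-grade endoscopy is coherent, as step 2 shows. No section says that subscore 2 patients were meant to be included, and a demanding healing endpoint is not an error. The strict sign may also be a slip confined to the article. All of this stands. It means that the documents do not show a strict contradiction, and it is why the remedy is to reconcile the passages and not to impose a threshold. It does not remove the point: the article gives one explicit threshold, and its plain meaning narrows the population in a way that the rest of the text never acknowledges.

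Several stronger readings are tempting but unsupported:
- A reader might take "The participants will be 120 patients with moderately active UC diagnosed as per histologic and endoscopic criteria" as a promise of moderate endoscopic grade. In context it most naturally concerns how UC is diagnosed, since the next sentence cites diagnostic guidelines.
- A reader might infer that the ten sites are applying the rule differently. The article describes a standardised screening form and regular discussion of the protocol at each subcentre, and gives no sign of divergence.
- A reader might infer that subscore 2 patients will be removed under Withdrawal criteria. Eligibility is screened before allocation, so that section matters only if the rule was misapplied.
- A reader might turn the counts in steps 2 and 3 into a share of patients excluded. They count score combinations, all weighted equally, and the article gives no distribution of endoscopic grades.
- A reader might say that the planning rates, which "would be 79% in the QCHS granule group and 41% in the placebo group", do not fit a top-grade population. They rest on cited work that is not shown, so this is conjecture.

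**Conclusion.** The point holds as a mismatch between cut-off and label. On whole-number grades 0 to 3, the written rule admits grade 3 only, and the article neither says that this is intended nor describes the population that way. The consequence for mucosal healing is definite on the literal rule: at least two grades of improvement in every patient. The consequence for the primary response depends on whether its subscore condition includes endoscopy. How many patients are affected cannot be stated from the article.

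A reader might conclude that the inequality is certainly a misprint, or that the two parts of the criterion are incompatible. The documents establish neither. The matter should be put right because it decides whom the result describes, but it does not threaten the validity of the randomised comparison.

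**What to change.** Reconcile the Inclusion criteria with the stated population, the full protocol (version 4.0) and the rule printed on the standardised screening form.

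- If sites admit subscore 2, correct the operator so that the text includes it.
- If only subscore 3 is eligible, keep the rule and do not change eligibility mid-trial. State that entry is restricted to the top endoscopic grade, and word the population and the conclusion to match.

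In either case, keep every randomised patient in the intention-to-treat analysis whatever the entry subscore, and report the baseline endoscopy subscore by arm so that readers can see whom the result describes.

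The cost is a short amendment and a check of screening forms for patients enrolled since April 2016.
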